### Design

This will be a stratified (gender, site), RCT of a the SSGT programme (KONTAKT©) compared to a manualised active control group (a cooking group “Super Chef”) with a ratio of 1:1, adhering to the CONSORT statement for conducting high-quality RCTs [48] (Fig. 1). Data collection will occur at three time points (1): at baseline, prior to randomization to intervention or control; (2) at post-test, immediately following the intervention period; and (3) at follow-up, 12 weeks following the intervention (primary endpoint).

**Fig. 1 Fig1:**
[figure not shown]
Participant recruitment, allocation, and assessment procedure

### Participants

Participants will be recruited through the Autism Association of Western Australia (AAWA) with the study promoted via newsletters, parent events, and social media. Informed consent/assent will be obtained from both parents and adolescents after receiving detailed verbal and written information about the programme, directions in case of adverse events, assessment timelines, and data collection procedures from a member of the research team at Curtin University.

### Inclusion criteria

The inclusion criteria for participating in this study will be as follows: (1) a clinical diagnosis of autism, Asperger syndrome, pervasive developmental disorder - not otherwise specified, or ASD according to the *Diagnostic and Statistical Manual of Mental disorders- version IV* (DSM-IV) [49], or ASD according to DSM-5 [1]. This will be further confirmed by administering the Autism Diagnostic Observation Schedule (ADOS-2) [50]; (2) an IQ > 70 on the Wechsler Abbreviated Scale for Intelligence (WASI-II) [51]; and (3) aged between 12 and 17 years at randomization.

### Exclusion criteria

Participants meeting the following criteria will be excluded from this study: (1) rule breaking and aggressive behaviours as confirmed by the Childhood Behaviour Checklist (CBCL) [52]; (2) prior clinically assessed, self-injurious behaviour; (3) low intrinsic motivation to participate; (4) insufficient English language skills; or (5) a history of clinically assessed self-injury, conduct disorder, hyperkinetic conduct disorder, antisocial personality disorder, borderline personality disorder, or any form of schizophrenia or related psychotic disorder that would interfere with participation or require alternative treatment.

Participants with common comorbid neurodevelopmental and psychiatric conditions such as attention problems, anxious or depressed behaviours as measured by CBCL [52] are acceptable in this trial as in previous evaluations of KONTAKT (c) [17, 32]. In addition, the participants may continue with their usual ongoing treatments or interventions.

### Sample size calculations

The KONTAKT© study in Sweden (both 12-week and 24-week versions) employed the Social Responsive Scale - second edition (SRS-2) as the primary outcome measure. Based on an effect size of 0.54, derived from roughly averaging the effect size (ES) as measured by the SRS-2 from trials examining the efficacy of the long 24-session (ES = 0.76) and the short 12-session (ES = 0.32) versions of KONTAKT© at post-test, and applying multivariate analysis of variance (MANOVA) for repeated measures (within-between interactions) at the three time points (using the intent-to-treat approach), a minimum of 57 participants are required (as calculated by G*Power [53] with power of 0.95 at a conventional error probability (α = 5%)). However, unlike the Swedish study, the present study will employ the Goal Attainment Scaling (GAS) as the primary outcome. It has been argued that GAS has good reliability when used as an outcome measure with interventions for adolescents with ASD [54–56]. Further, unlike previous investigation of KONTAKT© [17, 32], the current study will compare this SSGT efficacy against an active control group, to control for exposure to a social context with peers with ASD. It is likely that both these factors will have a limiting impact on the power of the study, and as such we will aim to recruit a sample of at least 90 participants into this study, increasing the likelihood of detecting possible effects [19]. This sample size will also account for an attrition rate of 37%, which is larger than what is expected based on the previous KONTAKT© studies.

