## Methods

### Aim

This protocol aims to employ an RCT design to rigorously evaluate the efficacy of KONTAKT© in supporting the attainment of personally meaningful social goals of adolescents with ASD. The design of this study will address many of the noted limitations of previous SSGT evaluation research, including implementation of a manualised intervention KONTAKT©, controlling for social context, employing a primary outcome measure with adequate power to assess the achievement of adolescents’ personally meaningful social goals, undertaking a cost utility analysis, and investigating the relationship between dose (number of sessions) and the response of adolescents with ASD to a SSGT intervention. The study design stipulates clear inclusion and exclusion criteria, standardised outcomes measures validated for use with adolescents with ASD, blinded assessment of outcome measures, and stratified randomization. This study seeks to answer two research questions (1): can KONTAKT© make a unique contribution to facilitate achievement of adolescents’ personally meaningful social goals above and beyond any support provided by the positive social context? (2) Is KONTAKT© cost-effective in comparison to an active control condition?

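### The minimum of 57 for 95% power is what G*Power returns when 0.54 is entered directly as f(V); the metric of 0.54 is not named, and read as a standardised mean difference it gives about 52% power with 57 and 72% with 90 at follow-up

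*Protocol article*

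**What the plan says.** The planning effect is introduced in Sample size calculations as follows: "Based on an effect size of 0.54, derived from roughly averaging the effect size (ES) as measured by the SRS-2". The two sources are "the long 24-session (ES = 0.76") and "the short 12-session (ES = 0.32) versions of KONTAKT© at post-test". The test used for sizing is a repeated-measures MANOVA, within-between interaction, at three time points, with "power of 0.95 at a conventional error probability (α = 5"%). The result is "a minimum of 57 participants are required (as calculated by G*Power [53] with power of 0.95").

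The same section then notes that GAS, not the SRS-2, is the primary outcome and that the comparator is active. It expects both to limit power, raises the target to at least 90, and says that this also covers 37% attrition. It gives no power for 90.

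The Aim describes the design as "employing a primary outcome measure with adequate power to assess the achievement" of the adolescents' goals. The Design section places the main assessment "at follow-up, 12 weeks following the intervention (primary endpoint"). Under Primary outcome measure, the GAS score of −2 is defined as the participant's current level.

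**The concern.** f(V) and a standardised mean difference d are different scales. For a single two-group contrast f = d/2, so f = 0.54 corresponds to d = 1.08, which is larger than even the 24-session effect of 0.76. An average of two published trial effect sizes is most naturally a d. The section names no metric, no conversion and no correlation, so the reader cannot tell whether the figure typed into the program meant what the routine takes it to mean.

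The stake is how the result is read. If 57 at 95% is taken as a sound base, and 90 as that base plus a margin, a null result at follow-up would be given more weight than the design supports. In addition, 0.54 is a post-test effect, while the primary endpoint lies 12 weeks later.

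**Working it through.** **Inputs.** From the protocol: effect size 0.54, two arms at 1:1, three measurements, α = 0.05, power 0.95, minimum 57, target 90, attrition 37%, GAS baseline −2. Assumed because not stated: 0.54 is a standardised mean difference, tests are two-sided, and the difference persists to follow-up. Between-visit correlation ρ is shown as a range.

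**1. The plan's own figure.** For f(V) with two groups and three measures, λ = N·f(V)², df1 = 2 and df2 = N − 3, using the noncentral F.
- N = 57: λ = 57 × 0.2916 = 16.62, power 0.9533.
- N = 56: λ = 16.33, power 0.9497.

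So 57 is the smallest N reaching 0.95, with no further input.

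**2. When d = 0.54 could equal f(V) = 0.54.** Take a difference of d at both post-baseline visits, a baseline free to vary, and equal correlation ρ between visits. Then f(V)² = d² / [6(1 − ρ)]. Setting f(V) = d gives 1 − ρ = 1/6, so ρ ≈ 0.83. Power in this setting depends heavily on ρ:

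| ρ | N = 57 | N = 90 |
|---|---|---|
| 0.3 | 0.39 | 0.59 |
| 0.5 | 0.52 | 0.74 |
| 0.6 | 0.62 | 0.84 |
| 0.7 | 0.76 | 0.93 |
| 0.8 | 0.91 | 0.99 |

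**3. Why that route is closed for GAS.** Every participant starts at −2, so baseline has no variance and change from baseline is just the later score plus 2. A high correlation with baseline cannot reduce the error.

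**4. GAS at follow-up only.** Two-sample t, d = 0.54:
- 57 analysed (28 and 29): noncentrality 0.54/√(1/28 + 1/29) = 2.04, power 0.52.
- 90 analysed (45 and 45): noncentrality 0.54/√(2/45) = 2.56, power 0.72.
- 95% power needs 91 per arm.
- 80% power is reached at d ≈ 0.60 with 90 and d ≈ 0.76 with 57.

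**5. GAS using both post-baseline visits.** With a fixed baseline and a difference of d at both visits, f(V)² = d² / [2(1 + ρ)], where ρ is now the correlation between post-test and follow-up.
- ρ = 0.3: f(V)² = 0.2916/2.6 = 0.112, f(V) = 0.33, power 0.59 at 57 and 0.80 at 90.
- ρ = 0.83: f(V)² = 0.2916/3.66 = 0.080, f(V) = 0.28, power 0.44 at 57 and 0.65 at 90.

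**6. Attrition.** 90 × 0.63 = 56.7, or about 57.

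No figure above allows for clustering within training groups.

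**The case against.** Four points can be made for the plan.

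First, the metric is inferred. The section says only effect size, and the source trials are not at hand. This stands, so the power figures are conditional.

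Second, a reader might infer that 57 can arise in no other way. That is not so. A conventional f = 0.27 (that is, d/2) with ρ = 0.25 gives λ = 57 × 3 × 0.0729/0.75 = 16.62, the same as above, and hence also 57. But this needs a correlation that appears nowhere in the protocol. It also takes 0.27 as the interaction effect, whereas a difference of 0.54 emerging after baseline and held at both visits has an interaction f of only 0.127.

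Third, the 57 is an SRS-2 calculation, and a high SRS-2 correlation could support it. The section itself concedes that GAS and the active control will limit power, and never claims 95% for GAS. This stands in part: the protocol does not hide the change of outcome. It nevertheless uses 57 as its base and claims adequate power for the primary outcome in the Aim.

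Fourth, the planned random-effects model includes age, IQ, gender, centre and comorbidity, which may add precision. If these had a multiple correlation of 0.3 with the GAS score, follow-up power would be about 0.56 at 57 and 0.76 at 90. The protocol gives no such value, and the gain is modest.

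**Conclusion.** The point holds in conditional form. The printed 57 matches 0.54 entered directly as f(V), and the protocol gives nothing to show that 0.54 is on that scale. If it is a standardised mean difference that persists to follow-up, power for GAS at 12 weeks is about 52% with 57 analysed and 72% with 90. Using both post-baseline visits, with a visit correlation of 0.3 to 0.83, power is about 44–59% and 65–80%. All figures are before clustering. The increase to 90 helps only if attrition stays well below the 37% that the protocol says it covers.

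Two stronger readings are not supported. One is that the trial will probably miss its own planning effect. At 90 analysed, detection is more likely than not on these figures, and the protocol describes 37% attrition as larger than expected. The other is that 0.54 should have been scaled down to match 16 sessions. That would require a linear dose-response drawn from two trials, and the protocol openly describes a rough average.

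**What to change.** Keep the target of 90. In Sample size calculations:
- State the metric of 0.54, the value entered in G*Power and any between-visit correlation assumed.
- Withdraw the minimum of 57 at power 0.95 unless the stated conversion supports it.
- Report power, or the detectable difference, for GAS at the 12-week follow-up as a range over stated assumptions, with 90 analysed and after the stated attrition. If 0.54 is a standardised mean difference, 80% power corresponds to d of about 0.60 with 90 analysed and about 0.76 with 57, before clustering.
- Say that 0.54 is a post-test effect assumed to persist to follow-up.

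In the Aim, bring the power claim into line with those figures.

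The cost is wording only. No participants, visits or analyses are added, but the stated power becomes less favourable.

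### The increase from 57 to 90 is claimed both for lower expected power and for 37% attrition, but attrition of 37% alone uses all of it

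*Protocol article*

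**What the plan says.** All of this is in the protocol article, Methods, Sample size calculations.

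- **Effect size.** "Based on an effect size of 0.54, derived from roughly averaging the effect size (ES) as measured by the SRS-2" in the earlier 24-session (0.76) and 12-session (0.32) trials.
- **Test and result.** The calculation assumes "multivariate analysis of variance (MANOVA) for repeated measures (within-between interactions) at the three time points". At power 0.95 and α of 5%, "a minimum of 57 participants are required".
- **First reason for going above 57.** The section names two departures from the earlier trials, the GAS outcome and the active control, and gives them as the ground for a larger target: "both these factors will have a limiting impact on the power of the study, and as such we will aim to recruit a sample of". The figure named there is 90 or more. The size of the expected reduction is not given.
- **Second reason.** The next sentence reads "This sample size will also account for an attrition rate of 37%, which is larger than what is expected" from the previous KONTAKT studies. The expected rate is not given.

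The section shows no reduced effect size, no intermediate sample size and no separate inflation step between 57 and 90.

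**The concern.** The 57 belongs to the effect of 0.54, which comes from trials with a different primary outcome and no active control. The protocol accepts that this is optimistic for the present trial: "It is likely that both these factors will have a limiting impact on the power of the study". The extra 33 participants are its answer to that. The word *also* in the following sentence then presents protection against 37% attrition as a further benefit of the same 90.

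For both to hold, some of the 33 would have to be left after 37% of the sample is lost. If none is left, the protocol claims a protection that the design does not have. A reader would take it that attrition of over a third still leaves room for a weaker effect against the active control. The Aim section counts adequate power for the primary outcome among the design's strengths, so the statement about what 90 protects against should be accurate.

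**Working it through.** **Inputs** (Sample size calculations and Design): effect 0.54 = (0.76 + 0.32)/2; two groups allocated "with a ratio of 1:1"; three time points; power 0.95; α = 0.05; minimum N = 57; target N = 90; attrition 37%.

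**Step 1: reproduce 57.** For the within-between interaction in a repeated-measures MANOVA with 2 groups and 3 time points, G*Power's form is a noncentral F with

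- df1 = (2 − 1)(3 − 1) = 2
- df2 = N − 3
- λ = N × f(V)²

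With f(V) = 0.54:

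- N = 57: λ = 57 × 0.2916 = 16.62, power 0.953
- N = 56: λ = 56 × 0.2916 = 16.33, power 0.9497

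So 57 is the smallest N that reaches 0.95, and the protocol's figure is reproduced exactly.

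**Step 2: where 37% comes from.**

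- 1 − 57/90 = 33/90 = 36.7%
- 90 × (1 − 0.37) = 56.7
- 57/(1 − 0.37) = 90.5

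The 37% is therefore the loss that takes 90 back to 57. It uses all 33 added participants.

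**Step 3: what is left for a smaller effect.** The table solves the Step 1 formula for the f(V) detectable at power 0.95, and gives the power if the true effect is 10% smaller (0.486) or 20% smaller (0.432) than 0.54. The attrition rates of 10% and 20% and both reductions are assumptions, because the protocol gives neither an expected attrition rate nor a reduced effect.

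| Analysed | Attrition from 90 | Detectable f(V) at 0.95 | Below 0.54 by | Power, effect 10% smaller | Power, effect 20% smaller |
|---|---|---|---|---|---|
| 90 | 0% | 0.422 | 22% | 0.987 | 0.959 |
| 81 | 10% (assumed) | 0.445 | 18% | 0.977 | 0.937 |
| 72 | 20% (assumed) | 0.473 | 12% | 0.960 | 0.905 |
| 57 | 37% (protocol) | 0.535 | under 1% | 0.902 | 0.818 |

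At 37% attrition the detectable effect is 0.535 against a planning value of 0.54, so the allowance for a smaller effect is gone. At 10% or 20% attrition, part of it survives.

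**Step 4: what both allowances together would take.** For an effect 10% smaller, power 0.95 needs 69 analysed, and 69/0.63 gives 110 recruited. For 20% smaller it needs 86 analysed and 137 recruited. These figures show the size of the gap and are not a proposal to enlarge the trial.

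**The case against.** **37% is a ceiling, not the planning rate.** The protocol says that this rate exceeds what it expects. Below it a margin exists, as the table shows. This stands. A reader might infer that 90 offers no margin at all, or that it can serve one purpose but never the other. The documents do not support that reading: at an assumed 20% attrition, power is still 0.960 for a 10% smaller effect and 0.905 for a 20% smaller one. The defect lies in claiming the full 37% on top of the power allowance.

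**No promise of 0.95 in the joint worst case.** For the first purpose the section claims only a better chance of detecting effects. This is fair and limits the weight of the point. Even so, the 37% is meaningful only as the loss that leaves 57, and 57 meets the power target only at the unreduced 0.54.

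**Participants who drop out may still contribute data.** The Data collection section provides for questionnaires by email, and Statistical analyses plans a random effects model under intent-to-treat. Treating 37% attrition as 57 complete cases is therefore conservative. That may soften the loss, but it does not create a second allowance, and the sample size section does not rely on it.

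**No number is wrong.** That is true: 57 reproduces and 37% is 36.7% rounded. The error is in what the numbers are said to cover. A reader might also infer that the protocol treats heavy attrition as harmless; it says nothing of the kind.

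**Conclusion.** Wrong as written. The same 33 participants are assigned to lower expected power and to 37% attrition, and attrition at that rate uses all of them. The trial would then be back at 57, with a detectable f(V) of 0.535 at power 0.95. Power would be about 0.90 for a 10% smaller effect and 0.82 for a 20% smaller one. At lower attrition the allowance is reduced, not lost.

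The overlap of 57, 90 and 37% is plain arithmetic and holds on any effect scale. The power figures and detectable effects hold only if 0.54 is an f(V), which is the reading that reproduces 57. The protocol does not state the scale. If 0.54 were a standardised mean difference, f would be about 0.27 and the same formula would give power of about 0.41 with 57 analysed and 0.61 with 90. That is a separate question, and the present point does not depend on it.

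**What to change.** In Sample size calculations:

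1. Delete the statement that the sample of 90 additionally covers 37% attrition.
2. State instead that attrition of 37% would use the whole increase from 57 to 90 and leave no allowance for a smaller effect.
3. Give the attrition rate expected from the earlier KONTAKT trials, and the effect detectable at power 0.95 with the number then analysed. On the protocol's own f(V) scale the reference values are 0.42 with 90 analysed, 0.445 with 81, 0.47 with 72 and 0.535 with 57. Say that they take 0.54 as an f(V).

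The replacement should not present the choice as either 37% attrition or a 22% smaller effect, because the intermediate cases are the ones the protocol expects.

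Cost: wording only. The recruitment target, design and analysis do not change. The downside is that the stated robustness to attrition becomes less favourable.

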### Setting

Participants expressing an interest in the study will be invited to a screening session and following determination of their eligibility will take part in a baseline assessment in a university laboratory at Curtin University, Perth, Western Australia. Both the KONTAKT© group and the active control cooking-group will be delivered by AAWA in one of their four metropolitan centres in Perth, Western Australia. The AAWA is the leading service provider for people with ASD in Western Australia, and the only specialist organisation providing a full range of services for children and adults in Australia, with over 700 multi-disciplinary staff.

### Randomization

Participants will be stratified for gender and then randomly allocated to either KONTAKT© (intervention group) or the Super Chef cooking-group (active control group) across AAWA centres. The randomization will be conducted by a statistician and sent directly to the AAWA study coordinator, supporting blind assessment of outcome measures by the research team.

### The interventions

In evaluating the feasibility and acceptability of KONTAKT© in an Australian context, a pilot version of the 16-session KONTAKT© was delivered to 16 adolescents meeting the inclusion criteria across 16 sessions in 20 weeks, with two 8-week session blocks interspersed with the Australian school holidays. After completing the KONTAKT© intervention, focus groups were held with participants, parents and trainers, capturing their perspectives of the programme. Following analysis of focus group data, final adjustments and modifications were made to the KONTAKT© 16-week variant, standardising the intervention in preparation for RCT evaluation. Tables 1 and 2 detail the structure and content of KONTAKT© (the opportunity to choose social themes/activities that reflect the participants’ personal goals or interests) and Super Chef (personal tastes for each recipe) sessions, and their emphasis on individualized activities aiming to promote motivation in the participants and generalization of skills [32].

**Table 1 Tab1:** The structure, objectives and individualized parts of weekly KONTAKT© sessions [57]

Rounds	Objective	Individualized activity
Opening	Warm-up activity, initiating conversation, promoting interaction between group members, promoting eye contact	
Reviewing homework	Reinforcing and providing feedback, troubleshooting if necessary	Sessions 2–15
Group discussion	Exchanging experiences, promoting social cognition and social relationship	Sessions 12–15
Group activities	Providing practical solutions and strategies for everyday challenging social situations, fostering a feeling of group cohesion, practicing cooperation, practising recognising and interpreting non-verbal signals, eye contact, and facial expressions	Sessions 12–15
Snack time	Practising small-talk and turn-taking in unstructured conversations	
Assigning new homework	Generalizing learnt skills to everyday social situations	Fixed: sessions 1–10 Flexible: sessions 11–14
Closing	Evaluating the session, promoting interaction between group members

**Table 2 Tab2:** The structure, objectives and individualized activities of weekly Super Chef sessions

Rounds	Objective	Individualized activity
Transition	Self-regulation and arrival into the session	
Activity 1	Sharing cooking experiences	
Activity 2	Preparation for cooking and food exploration	Every session
Snack time	Practicing small-talk and turn-taking in unstructured conversation, participating in games and activities	
Activity 3	Cooking or baking	Every session
Eating the prepared meal	Rating the prepared meal	
Clean up	Washing up, drying dishes, wiping down benches and tables, and sweeping the floor.	Every session
Transition	Recapping the session and feedback to the parents	

The Australian adaptation of KONTAKT©, employing a 16-session variant, aims to improve participants’ communication and social interaction skills, ASD-related traits, and the ability to empathise and adapt in a group setting of 6–8 adolescents aged 12–17 years [19, 21]. Groups meet weekly for an hour and a half, with two trainers delivering a programme underpinned by the principles of cognitive behaviour therapy, behaviour activation, observational learning, psychoeducation, and social cognition training [41, 42]. Sessions scaffold knowledge of common social rules and norms, aiming to promote problem-solving strategies, emotion recognition, and emotion expression [19].

KONTAKT© requires that at least one group trainer is a clinician with extensive experience working with children/adolescents with ASD, who has also received methodological training, or certification in KONTAKT© prior to the programme. Prior to the pilot, Australian clinicians from AAWA were trained by a Swedish team of certified KONTAKT© trainers. Requirements of KONTAKT© training certification include passing this method training, leading at least one KONTAKT© group under supervision, and achieving intervention fidelity as assessed by a KONTAKT© supervisor on the basis of submission of a filmed KONTAKT© session. A KONTAKT©-certified trainer can, in turn, instruct others in delivering KONTAKT©. In the present study, fidelity to the KONTAKT© intervention will be systematically assessed by trainers completing a session by session fidelity checklist, enabling an assessment of intervention fidelity. In addition, attendance sheets will be kept to record the participants’ compliance with the programme, with 80% attendance considered as compliant.

Super Chef is a manualised cooking-group programme specifically designed for this study (Table 2), with the goal of enabling comparison of KONTAKT© with an active social control group, enabling independent evaluation of the contribution of KONTAKT© to intervention outcomes. As in KONTAKT©, participants allocated to the Super Chef programme will meet weekly in groups of 6–8 for an hour and a half in a 16-session programme moderated by two trainers, one of which will be an occupational therapist with previous experience of working with Australian adolescents with ASD. As with KONTAKT©, each Super Chef session adheres to a specified agenda including discussions, taste testing, individual and group activities, snack time, cooking recipes, eating and rating recipes and cleaning up as rostered. Super Chef was developed by a team including occupational therapists with both clinical and research experience in working with adolescents with ASD, with consideration of the common sensory issues associated with ASD. Fidelity to the Super Chef intervention will be assessed via a fidelity checklist, specially designed for this programme, enabling assessment of the extent to which trainers followed the format of each session.

